### 2.4. Interventions

The patients receive the same radiotherapy or chemoradiation for lung cancer as they would have received without participation in the POLCAR trial. Radiotherapy is performed as volumetric-modulated arc therapy using conventional fractionation with doses per fraction of 2.0 Gy given five consecutive days per week and total doses ranging between 60 and 70 Gy [2]. The patients in this trial may receive any medical support required for adverse events, co-morbidities, or other conditions. Trial-specific interventions include completion of a paper-based questionnaire (symptom-based scoring system) once a week during and up to 24 weeks following radiotherapy and completion of a questionnaire rating the patient satisfaction with the symptom-based scoring system at the end of the radiotherapy course. The follow-up period of 24 weeks was chosen according to the results of previous studies showing that pneumonitis can occur up to 23 weeks following radiotherapy [4,5]. The English version of the questionnaire was properly translated into the languages of the participating centers.

The patients indicate and rate symptoms potentially caused by radiation pneumonitis, i.e., cough, dyspnea, and fever (Table 3), once a week by completing a paper-based questionnaire. During the radiotherapy course, the patients complete the questionnaire at the department of radiotherapy. After completion of radiotherapy, the information regarding the symptoms potentially related to pneumonitis will be obtained weekly by phone (to minimize hospital visits). The procedure of the telephone visits is clear, and uniformity is ensured. Support from caregivers is not allowed. Since the patients are contacted actively by staff members, the risk of loss to the follow-up is comparably low. In our previous trial, the rate of termination of follow-up due to the patient’s unavailability was 8.8% [6].

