If the total score is higher than at baseline prior to the start of radiotherapy, the patients receive a follow-up call after 3 days or are asked to present at the corresponding hospital. If pneumonitis is suspected, the patients undergo lung function tests. The suspected diagnosis of pneumonitis is considered substantiated in case of a decrease in forced expiratory volume in 1 s (FEV1) and diffusing capacity of the lung for carbon monoxide (DLCO) to less than 75% from baseline values [16,17]. In this situation, the patients receive a chest X-Ray (which may be supplemented by a computed tomography). Radiation pneumonitis is considered confirmed if opacities confined to the irradiation fields are seen on chest X-Ray and/or ground-glass opacities (focal or nodular), consolidation, or both are seen on computed tomography [18,19]. The imaging findings are interpreted by experienced radiologists. If the diagnosis of pneumonitis grade ≥ 2 (CTCAE v5.0) is made, the patients generally receive treatment with prednisolone [5,16,20]. If the symptoms are caused by a medical condition other than pneumonitis, the patients are treated for this situation. Finally, the total score of the symptom-based scoring system is correlated to pneumonitis (yes or no). Since the scoring tool is easy to use, consistent assessment across multiple centers appears secured. This assumption is supported by the experiences from a previous prospective trial [6].

At the end of the radiotherapy course, the patients will complete a questionnaire regarding their satisfaction with the paper-based version of the scoring system, modified according to the User Experience Questionnaire, a widely used and reliable tool [21,22]. If the dissatisfaction rate is >20%, the scoring system needs to be modified, and if the dissatisfaction rate is >40%, it is considered not useful. If patients withdraw their consent to participate in the trial, study-specific interventions are stopped. In case of adverse events, which do not allow patients to complete subsequent questionnaires, study-specific interventions are postponed or discontinued, if necessary.

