### 2.6. Statistical Methods for Primary and Secondary Outcomes

#### 2.6.1. Primary Objective

The primary objective is to assess the performance characteristics of the symptom-based scoring system for the detection of radiation pneumonitis. An evaluation will be performed in patients available for assessment of the primary endpoint who have completed at least 10 questionnaires regarding their symptoms. To allow for patient-based analyses, the multiple score values documented for each patient over time will be reduced to one clinically relevant, patient-specific value only. Thus, for patients without radiation pneumonitis during the study, the maximum score value documented throughout the study will be used, and for patients with pneumonitis, we use the value documented at the time of diagnosis. These patient-specific values represent the fundamental units for all further statistical analyses. First of all, sensitivity and specificity will be estimated for every possible cut-off value of the symptom-based scoring system.

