Due to the limited sample size that could be realistically achieved in this multi-center trial within the given study duration, it was not considered feasible to develop and validate the optimal cut-off value identified within this single study at the same time by dividing the study population into training and validation cohorts. Therefore, the derived cut-off value should be considered a preliminary suggestion, which should be validated in subsequent studies. As a further sensitivity analysis, the relationship between tertiles of the symptom-based scores and the incidence of radiation pneumonitis will be statistically tested using the Jonckheere–Terpstra test, which is a nonparametric test for ordered differences among groups of score values [27,28,29]. It tests the global null hypothesis that the distribution of the response variable does not differ among tertiles. The test is designed to detect alternatives of ordered differences, meaning that the incidence of pneumonitis increases with the tertiles of score values. In addition, the impact of potential risk factors, including radiation dose, co-morbidity (particularly significant cardiovascular disease), history of smoking, radiation doses, and concurrent medication including chemotherapy and immunotherapy on the prevalence of pneumonitis, will be evaluated [4]. The histology of lung cancer (NSCLC or SCLC) was not associated with pneumonitis in previous studies and, therefore, its potential impact will not be separately analyzed [4,6,14].

Based on the participation of highly committed study sites only and our previous trial experience, the rate of missing data can be assumed to be rather low. Furthermore, the primary endpoint consists of the derivation of one patient-specific value from the multiple score values documented during each visit. Based on the scientific question of interest in this single-arm trial, missing values will not be imputed regardless of any intercurrent events (“treatment policy strategy”).

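### Scores missed through illness can only leave specificity unchanged or overstate it, because non-cases are scored by their recorded maximum and missing weeks are ignored

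*Protocol article*

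**What the plan says.** Four rules in the protocol article act together.

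- **Collection (Section 2.4):** "In case of adverse events, which do not allow patients to complete subsequent questionnaires, study-specific interventions are postponed or discontinued, if necessary". The weekly symptom questionnaire is one of these study-specific interventions. After radiotherapy it is taken by telephone, and caregivers may not help.
- **Value analysed (Section 2.6.1):** "for patients without radiation pneumonitis during the study, the maximum score value documented throughout the study will be used", whereas "for patients with pneumonitis, we use the value documented at the time of diagnosis".
- **Who is evaluated (Section 2.6.1):** patients "who have completed at least 10 questionnaires regarding their symptoms". Radiotherapy lasts 6–7 weeks and follow-up 24 weeks, so about 30 weekly questionnaires are planned.
- **Missing scores (Section 2.6.1):** "missing values will not be imputed regardless of any intercurrent events", under a treatment policy label. Two reasons are given: "the rate of missing data can be assumed to be rather low", with no figure attached, and each patient contributes only one derived value.

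Section 2.4 gives 8.8% as the share of patients in the previous trial whose follow-up ended because they could not be reached. The article states no rule for a case who has no score at diagnosis.

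**The concern.** Section 2.6.1 treats the reduction to one value per patient as a reason why gaps matter little. For a maximum the opposite holds, since it depends entirely on whether the worst week was recorded. Cough, shortness of breath and fever are the scored items (Table 3), so in a non-case with acute respiratory illness the weeks most likely to be missed may be those with the highest points. Such a patient would then be scored from the weeks in which he or she was well.

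These patients matter most to the trial's purpose, which the Introduction and Conclusions describe as separating pneumonitis from other lung diseases. At stake are specificity at every cut-off, the positive predictive value (which Section 2.6.2 says can be estimated without bias), and the choice of cut-off against the 80% specificity criterion. If specificity is inflated, that criterion is met at an equal or lower cut-off than complete data would allow.

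**Working it through.** **1. Denominators.** Section 2.5 plans 59 patients, 18 with and 41 without pneumonitis. That figure reproduces from its inputs (AUC 0.9, lower bound 0.7, two-sided 5%, assurance 80%, ratio R = 2.33):

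- cases = (1.96·√V₀ + 0.842·√V₁)² / (0.9 − 0.7)²
- binormal variance V = 0.0099·exp(−a²/2)·[(5a² + 8) + (a² + 8)/R], with a = 1.414·z(AUC)
- V₀ (AUC 0.7) = 0.1084 and V₁ (AUC 0.9) = 0.0561
- cases = (1.96 × 0.3293 + 0.842 × 0.2368)² / 0.04 = 17.84; total = 17.84 × 3.33 = 59.4

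The point below does not affect the sample size. It uses only the 41 and the 18.

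**2. Direction for non-cases.** Let M be a patient's maximum over all planned weeks and M* the maximum over recorded weeks. Recorded weeks are a subset, so M* ≤ M. Specificity at cut-off c is the share of non-cases scoring below c, so replacing M by M* can only keep or raise it. This holds for non-cases who stay in the analysis. Because 10 questionnaires suffice, a non-case may be scored on 10/30 = 33% of the planned weeks.

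**3. Size for specificity.** One lost peak above the cut-off adds 1/41 = 2.4 points. The 80% criterion needs at least 0.80 × 41 = 32.8, that is 33 patients.

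| Lost peaks | Reported specificity if the true value is 31/41 |
|---|---|
| 0 | 31/41 = 75.6% |
| 1 | 32/41 = 78.0% |
| 2 | 33/41 = 80.5% (criterion met) |
| 3 | 34/41 = 82.9% |

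The starting value 31/41 and the counts of lost peaks are assumptions.

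**4. Positive predictive value.** Assume 16 of 18 cases lie above the cut-off. With 10 false positives the value is 16/26 = 61.5%. With two of them unrecorded it is 16/24 = 66.7%.

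**5. Cases.** If a high-scoring case has no score at diagnosis and drops out, it leaves numerator and denominator together: 17/18 → 16/17 is −0.3 points, 16/18 → 15/17 is −0.7, and 15/18 → 14/17 is −1.0. Sensitivity falls, but by little per patient.

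**6. AUC.** The AUC is the average over 18 × 41 case/non-case pairs. Start from the planned 0.900.

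- One non-case peak lost, assuming cases then outrank that patient with probability 0.92 instead of 0.50: + 0.42/41 = +0.010, giving 0.910.
- One case lost that outranked every non-case: (18 × 0.900 − 1)/17 = 0.894.
- One non-case peak and one such case lost: (18 × 0.9102 − 1)/17 = 0.905.
- One non-case peak and two such cases lost: (18 × 0.9102 − 2)/16 = 0.899, below the start.

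An illustrative simulation of weekly scores, with assumed distributions and a cut-off of 5, shows the same pattern:

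| Non-case peaks lost | High-scoring cases lost | Specificity | Sensitivity | AUC |
|---|---|---|---|---|
| 0% | 0% | 0.745 | 0.837 | 0.855 |
| 25% | 0% | 0.770 | 0.837 | 0.873 |
| 0% | 50% | 0.745 | 0.800 | 0.830 |
| 25% | 50% | 0.770 | 0.800 | 0.850 |
| 50% | 50% | 0.796 | 0.800 | 0.871 |

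Specificity never moves down. The AUC moves either way.

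**The case against.** The case for leaving the plan alone has real substance.

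- **The rule is narrow.** Section 2.4 covers adverse events that prevent completion, and acts only where necessary. A reader might infer that scoring stops whenever a patient is ill. The text does not say so: the instrument has three items, staff take it by phone, and contact is daily on treatment days and weekly afterwards. This limits the number of lost weeks but does not remove them, because no proxy is permitted. The extra call after 3 days is triggered by a recorded rise, which is the very value that would be missing.
- **Cases should rarely lack a score.** Work-up follows a score above baseline and needs lung function tests. A patient able to perform these can usually answer three questions. This stands, and it makes the loss of cases the smaller worry.
- **AUC.** A reader might infer that the AUC is overstated and the whole analysis tilted towards the score. Steps 5 and 6 show why that does not follow: lost cases pull sensitivity and AUC down, and the balance is unknown. A reader might also put each lost case at 1/18 = 5.6 points of sensitivity. That would need the case to be kept and counted as a miss, which the plan does not say.
- **The cut-off is provisional.** Section 2.6.1 says it needs validation. That is true, but a provisional cut-off should still not be chosen on a specificity biased in a known direction.
- **A separate analysis plan may add sensitivity analyses.** It may, but it cannot recover scores that nobody asked for, and the article itself fixes the no-imputation rule and its rationale.

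**Conclusion.** The point holds for specificity. Under the stated rules, scores missed through illness in non-cases who remain in the analysis can only leave specificity unchanged or overstate it, and at a given cut-off unrecorded false positives likewise inflate the positive predictive value. Each lost peak is worth 2.4 points with 41 non-cases, and two are enough to cross the 80% criterion from 31/41. The number of such patients cannot be derived from the document, so the direction is firm and the size is not.

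No direction can be claimed for the AUC, and the primary test against 0.7 is not shown to be at risk. Two statements in Section 2.6.1 do not stand as written. Deriving one value per patient does not make gaps unimportant when that value is a maximum. The treatment policy label also does not fit where collection may stop, since that strategy relies on values observed after the event.

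**What to change.** 1. In Section 2.4, add that at the first contact after a missed week the patient is asked for the worst cough, shortness of breath and fever of that week, scored with Table 3 and flagged as recalled.
2. In Section 2.6.1, use the flagged score in the maximum for non-cases and, for a case with no score at diagnosis, as the value at diagnosis.
3. Report AUC, specificity and cut-off with and without flagged values, with the number of non-cases whose gaps could not be filled and the number of cases without a score at diagnosis.
4. Delete the argument that one value per patient makes missing scores unimportant. Keep the treatment policy label only where scores are collected after the event.

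Any use of the CTCAE adverse event records to fill remaining gaps should be exploratory only: Table 3 points are the patient's own ratings, and the article gives no mapping from CTCAE grades to points.

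The cost is one line on the weekly form, a sentence or two in each section and one repeat of the analysis. The drawback is that recalled scores are less exact, which is why they are flagged and results are shown both ways.

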#### 2.6.2. Secondary Objectives

The secondary objective is to determine positive and negative predictive values associated with each scoring point of the symptom-based scoring system. The positive predictive value is the probability that subjects with a high symptom score truly suffer from radiation pneumonitis. The negative predictive value is the probability that subjects with a low symptom score truly don’t suffer from pneumonitis. Thus, the predictive values describe the performance of the scoring system and the relevance for the subjects, whereas sensitivity and specificity describe the intrinsic validity of the test criterion. Since the incidence of subjects experiencing pneumonitis observed in this study reflects the incidence of the target population with the specific inclusion/exclusion criteria (i.e., the number of subjects with pneumonitis is not pre-specified), the positive and negative predictive values for each potential cut-off can be estimated unbiasedly. Point estimates of positive and negative predictive values will be presented.

Patient satisfaction with the symptom-based scoring system is assessed at the end of radiotherapy. Statistical analysis consists of presenting the respective proportions. In case of a dissatisfaction rate >20%, the symptom-based scoring system needs modifications before it can be used in future studies. In case of a dissatisfaction rate >40%, the scoring system will be considered not useful.

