### 2.5. Sample Size Calculations

The main goal of this trial is to evaluate the usefulness of a new symptom-based scoring system with respect to the identification of elderly lung cancer patients developing pneumonitis after radiotherapy. The discriminative power of the symptom-based score will be assessed by calculating the AUC. The sample size is calculated to achieve acceptable precision in the estimation of the AUC measured by means of the 95% confidence interval by incorporating a pre-specified probability, which is referred to as assurance, of achieving the desired lower confidence limit [23].

The sample size calculations are based on a two-sided significance level of 5%, an AUC of 0.9, a pre-specified lower bound of the confidence interval of 0.7, an assurance probability of 80%, a ratio between negative and positive cases of 2.33 (70% of patients without and 30% with radiation pneumonitis). Based on these assumptions, 59 patients (18 with and 41 without radiation pneumonitis) are required within the Full Analysis Set. Assuming that 5% of patients will not qualify for the Full Analysis Set, a total of 62 patients should be enrolled. The drop-out rate includes patients who experience difficulties in completing questionnaires due to neurocognitive decline during the study period. The Full Analysis Set includes all the subjects who started radiotherapy.

A pneumonitis rate of 30% has been considered appropriate for the sample size calculation since, in a previous retrospective study investigating elderly patients irradiated for lung cancer, 27.3% of the patients developed pneumonitis [14]. Moreover, this rate is expected to be higher in the POLCAR trial due to the weekly assessment of pneumonitis for 24 weeks compared to the standard follow-up consisting of one visit about 6–8 weeks following radiotherapy only. All the lung cancer patients aged ≥ 65 years will be screened at each participating center. The recruitment of all 62 patients should be completed within 15 months. The treatment period will be 6–7 weeks, and the follow-up period 24 weeks. This equals a total running time for the trial of 22 months.

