Non-parametric methods for AUC estimation and testing using the normal approximation of the asymptotic properties of the AUC with standard errors derived by the DeLong, DeLong, and Clarke-Pearson method will be applied [24]. Technically, the SAS version 9.4 (SAS Institute Inc., Cary, NC, USA) LOGISTIC procedure with the ROCCONTRAST statement can be used to estimate the AUC and its 95% confidence limit and to provide the *p*-value for the test mentioned above. A significance level of two-sided 5% is prespecified. If the statistical significance of the AUC is reached, the most informative (optimal) scoring point to predict pneumonitis will be established. Based on discussions with experts, optimality is defined as a score cut-off value of at least 90% and specificity of at least 80%. In addition to this visual selection of a suitable cut-off value, the Youden index (sensitivity + specificity − 1) will be applied to propose an optimal cut-off value for further consideration [25,26].

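### Predictive values at each score are planned as point estimates with no interval named, although with about 18 cases the PPV near the target cut-off has a 95% interval roughly 39 points wide

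*Protocol article*

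**What the plan says.** Section 2.6.2 of the protocol article plans PPV and NPV for every scoring point. It argues that, because the number of cases is not fixed by design, "the positive and negative predictive values for each potential cut-off can be estimated unbiasedly". It then states the output: "Point estimates of positive and negative predictive values will be presented".

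Section 2.6.1 treats the primary measure differently: the AUC is to be estimated with a 95% confidence limit. Section 2.5 sizes the trial on the lower limit of that interval and expects 18 patients with and 41 without pneumonitis.

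The cut-off is chosen on the same patients. Section 2.6.1 says "optimality is defined as a score cut-off value of at least 90% and specificity of at least 80"%, and adds the Youden index. The word for what must reach 90% is missing; I read it as sensitivity. The same section explains that no separate validation cohort is feasible, calls the resulting cut-off preliminary and asks for validation in later studies.

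**The concern.** The article names intervals where it intends them, for the AUC, and for the predictive values it names point estimates. These are the figures that Section 2.6.2 itself links to relevance for the subjects. They say how often a high score means pneumonitis and how often a low score rules it out. With about 18 cases, a bare PPV of two in three or nine in ten cannot be read without its uncertainty, and a table of ten scores invites comparison of values that the data cannot separate.

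A smaller matter of wording goes with this. The unbiasedness sentence sits beside a plan that picks a cut-off on the same data, and the caution given for that cut-off is not expressly carried over to its predictive values.

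**Working it through.** **Inputs.** From Section 2.5: 18 cases and 41 non-cases, 59 in all; 30% of patients as cases, hence 2.33 non-cases per case; assurance 80%; alpha 0.05 on two sides; and, for the curve itself, "an AUC of 0.9, a pre-specified lower bound of the confidence interval of 0.7". From Section 2.6.1: the 90%/80% target.

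**1. The plan's own number.** Require 0.9 − 0.7 ≥ 1.960·SE(AUC = 0.7) + 0.842·SE(AUC = 0.9), with Hanley–McNeil standard errors.
- 17 and 40: 1.960 × 0.0801 + 0.842 × 0.0526 = 0.201, just too large.
- 18 and 41: 1.960 × 0.0780 + 0.842 × 0.0512 = 0.196, sufficient.

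This formula gives the stated 18 + 41 = 59. If the ratio of 2.33 is rounded up (2.33 × 18 = 41.9, so 42), it gives 60. Other variance formulas and scales gave totals from 34 to 160, so this is one reading that fits. The check below needs only the 18 and 41.

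**2. Predictive values near the target.** At least 90% of 18 is 16.2, so the smallest passing count is 17. At least 80% of 41 is 32.8, so it is 33. False positives are 41 − 33 = 8 and false negatives 18 − 17 = 1.
- PPV = 17/(17 + 8) = 17/25 = 68.0%
- NPV = 33/(33 + 1) = 33/34 = 97.1%

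Exact (Clopper–Pearson) limits for x out of n are the 2.5% quantile of Beta(x, n − x + 1) and the 97.5% quantile of Beta(x + 1, n − x).

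| Measure | Estimate | Exact 95% CI | Width (points) | Wilson 95% CI | Width (points) |
|---|---|---|---|---|---|
| PPV 17/25 | 68.0% | 46.5–85.1% | 38.6 | 48.4–82.8% | 34.4 |
| NPV 33/34 | 97.1% | 84.7–99.9% | 15.3 | 85.1–99.5% | 14.4 |
| Sensitivity 17/18 | 94.4% | 72.7–99.9% | 27.2 | 74.2–99.0% | 24.8 |
| Specificity 33/41 | 80.5% | 65.1–91.2% | 26.1 | 66.0–89.8% | 23.8 |

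**3. Other scores.** PPV and NPV denominators add to 59 at every cut-off, so when one grows the other shrinks. Exact widths at extreme cut-offs: PPV 9/10, 44 points; PPV or NPV 5/5, 52 points; PPV 3/3, 71 points.

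**4. Choosing the cut-off on the same data.** The documents give no score distribution, so one has to be assumed: 59 patients, 30% with pneumonitis, a ten-level score cut from two normal distributions with underlying AUC 0.8 or 0.9, 40,000 simulated trials each. Bias is the observed value minus the true value at the cut-off used.

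| Cut-off | AUC | PPV bias (points) | NPV bias (points) |
|---|---|---|---|
| Youden, same data | 0.8 | +3.9 | +2.5 |
| Youden, same data | 0.9 | +2.9 to +3.0 | +1.8 |
| Fixed in advance | 0.8 and 0.9 | under 0.1 in size | under 0.1 in size |

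The optimism is real, but small beside a PPV interval of 34 to 39 points.

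**The case against.** The sentence in Section 2.6.2 does not exclude intervals, and Section 2.7 refers to a pre-defined statistical analysis plan that is not shown. An interval method for descriptive secondary results is often left to such a plan, and the AUC gets an interval because it is the tested primary measure. The first part stands: a reader might infer that intervals are ruled out, and the text does not say so. But the article does state what will be presented, so the recommendation improves a stated presentation and does not fill a silence.

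Several stronger readings are tempting and are not supported.
- *That the unbiasedness statement is wrong.* It is argued from cohort sampling and concerns each potential cut-off. For a cut-off fixed in advance it is about right, as step 4 shows. Section 2.6.1 already calls the selected cut-off preliminary. What is missing is only an explicit link from that caution to the predictive values.
- *That about 40 points is the width for every predictive value, or the maximum.* It describes PPV, by the exact method, at one assumed operating point. NPV there is under 20 points, and extreme scores can exceed 40.
- *That restricting the evaluation to patients with at least 10 questionnaires distorts the case fraction.* This is possible, but the documents give nothing from which to size it, and they describe active weekly contact.
- *That the satisfaction result needs an interval to be decided.* For satisfaction, "Statistical analysis consists of presenting the respective proportions", and the 20% and 40% rules act on the observed rate. An interval would inform the reader but would not change the planned decision.
- *That this trial's PPV will set when the home application sends a patient to hospital.* The Introduction says that symptom ratings in a future application will contribute to that decision, and validation is to come first.

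For sensitivity and specificity, Section 2.6.1 says only that they will be estimated. Intervals there are a sensible companion, not the correction of an error.

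**Conclusion.** The point holds as a reporting matter. At the plan's expected numbers, a PPV of 68% near the target is compatible with anything from 46.5% to 85.1%, so the data could not exclude that fewer than half of high scores are true pneumonitis. NPV is better determined (84.7–99.9%). At sparse scores the intervals can exceed 50 points. Predictive values at a cut-off chosen on the same data are also optimistic by roughly 2 to 4 points.

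These figures assume that all 59 patients are analysed with 18 cases, that the 90% means sensitivity, and that the cut-off just meets both targets. The optimism rests on an assumed score distribution. The primary AUC test and its interval are untouched. The change is worth making, but the validity of the trial does not depend on it.

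**What to change.** In Section 2.6.2, replace the sentence on point estimates by: *PPV and NPV at each cut-off will be presented with exact (Clopper–Pearson) or Wilson 95% confidence intervals, and sensitivity and specificity likewise.* One of the two methods should be named before the data are seen.

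Add two clarifications. First, the unbiasedness statement holds for cut-offs fixed in advance, such as the 5 points of the earlier trial. Second, the caution in Section 2.6.1 (preliminary, to be validated) also covers predictive values at the cut-off selected on the same data, which tend to be optimistic.

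The cost is a few sentences and standard software output, with no extra patients, visits or data. The only drawback is a longer table.
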